### Study participants

The study will include individuals who meet all the following criteria:

➢ They are a primary caregiver with responsibility for a child under the age of 2.5 years (if the child is removed from the parents during the study, the intervention will continue on the premise that the child will be returned).

➢ They are receiving treatment for a drug or alcohol problem including opioid replacement treatment, relapse prevention or other treatment programme. If both parents have an alcohol or drugs problem, only the mother will be assessed.

➢ They are able to understand spoken English.

The following individuals will be excluded from the study:

➢ Parents whose child is not residing with them and does not have contact with them at the beginning of the intervention and where there is no plan for reunification.

➢ Pregnant women (unless the baby is due within 4 weeks of the recruitment period) who have no other child under 2.5 years residing with them.

➢ Women in a relationship in which there is active and ongoing domestic abuse or who are actively psychotic or expressing active suicidal ideation.

### Sample size

Dawe and Harnett [9] found an effect size (ES) of 0.92 using the Child Abuse Potential Inventory (CAPI) scores, in an RCT of the PuP programme in Australia with parents of children aged 3 to 8 years. This is a large change and the current study, which is being conducted with a younger population of children (under 2.5 years), should therefore be powered to detect a much smaller change.

Power calculations for the current study show that in the region of 54 women are required in each arm of the study to detect a change in the region of 0.5 ES with 80% power and 0.05 significance. Considerably more families (that is, in excess of 147 per arm) would be required to be confident of detecting a change that is smaller than this (that is, 0.45 ES). Allowing for dropout in the region of 5% [9] necessitates that approximately 114 families are recruited to the study (that is, 57 in each arm).

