#### *Primary analysis*

Changes in the CAPI score between baseline and at the 6-month follow-up will be compared for the intervention groups using ANCOVA with the site where the family was recruited used as an independent confounder.

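### The stated 54 per arm does not give 80% power for an effect size of 0.5: a two-sided 5% comparison has about 73% power and would need 64 per arm.

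*Protocol article*

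**What the plan says.** The Sample size section states that about "54 women are required in each arm of the study to detect a change in the region of 0.5 ES with 80% power", at "0.05 significance". It does not say whether the test is one- or two-sided, which test was assumed, or whether a baseline correlation was used. The next sentence puts the requirement for an effect size of 0.45 at more than 147 per arm. "Allowing for dropout in the region of 5"% then leads to "approximately 114 families are recruited to the study (that is, 57 in each arm").

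The Primary analysis section says that changes in the CAPI score from baseline to the 6-month follow-up "will be compared for the intervention groups using ANCOVA with the site where the family was recruited used as an independent confounder". Site is the only covariate named there.

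**The concern.** The article prints an effect size, a power and a significance level, and beside them a sample size that does not follow from them. The shortfall is 10 women per arm, about 16% of the 64 required.

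The figure has consequences. It fixes recruitment at 57 per arm, 114 in total and about 19 per centre, and it is the only basis the article gives for interpreting a null primary result. The same section says the trial should be able to detect a much smaller change than the 0.92 seen in the earlier trial, so sensitivity at 0.5 is the declared aim. If power there is 73%, the chance of missing a true effect of that size is 27% and not 20%.

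**Working it through.** **Inputs, all from the Sample size section:** effect size d = 0.5, power 80%, significance 0.05, two equal arms, 54 evaluable per arm, dropout 5%. Sidedness is not given; I take two-sided as the convention and also show one-sided.

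**1. Attempt to reproduce 54, two-sided.** With the normal approximation,

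n per arm = 2 × (1.960 + 0.842)² / d² = 2 × 7.849 / 0.25 = 62.8, so 63.

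The exact noncentral-t calculation gives 63.77, so 64. Neither gives 54.

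**2. Power with 54 per arm, two-sided.** Normal approximation: Φ(0.5 × √(54/2) − 1.960) = Φ(0.638) = 73.8%. Exact t-test: 73.1%. With all 57 recruited and no dropout, the exact figure is 75.4%.

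**3. Effect detectable with 80% power at 54 per arm.** Normal approximation: 2.802 × √(2/54) = 0.539. Exact t-test: 0.544.

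**4. One-sided 0.05.** The exact requirement is 50.15, so 51 per arm, and 54 would give 82.6%. This does not yield 54 either.

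**5. Dropout step.** 54 / 0.95 = 56.8, so 57 per arm and 114 in total. This is correct, so 54 is the evaluable number and the discrepancy arises before the dropout allowance.

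**6. Does a baseline correlation explain it?** Suppose 0.5 is in units of the SD of the score, and r is the correlation between the baseline and 6-month scores. Baseline-adjusted ANCOVA multiplies the required n by (1 − r²); an analysis of change without baseline adjustment multiplies it by 2(1 − r). For ANCOVA at r = 0.40: 63.77 × (1 − 0.16) = 53.6, so 54. The documents give no value of r for this interval, so the range below is an assumption.

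| r (assumed) | Power at 54 per arm, baseline-adjusted ANCOVA | Power at 54 per arm, change score without baseline |
|---|---|---|
| 0.3 | 77% | 59% |
| 0.4 | 80% | 65% |
| 0.5 | 84% | 73% |
| 0.6 | 90% | 82% |

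(Two-sided 5%, t-test, with effect sizes 0.5/√(1 − r²) and 0.5/√(2(1 − r)).)

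**7. Cross-check against the companion figure.** Required n is proportional to 1/d². Moving from 0.5 to 0.45 multiplies it by (0.5/0.45)² = 1.23, so 54 would become about 67. A fixed sidedness, power or correlation cancels from this ratio. The article's two figures differ by a factor of 147/54 = 2.7. Taken directly, d = 0.45 at 80% power, two-sided, needs 78.5, so 79 per arm; 147 per arm would give 97% power at 0.45, or 80% power at about 0.33. No single set of assumptions produces both 54 and 147.

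**The case against.** The strongest reply is that the planned analysis is ANCOVA and not a t-test. ANCOVA of a baseline-to-follow-up change is often run with the baseline score as covariate, and a condensed article may leave the covariate list to the analysis plan. With baseline in the model and r of about 0.40 or more, 54 per arm reaches 80%. The article quotes a 1-month test-retest stability of .83 for the full CAPI. That cannot be carried over to the brief form and a much longer interval, but a correlation of 0.40 is not implausible. This stands as a possible justification, and true power may be 80% or better. It does not make the printed statement follow from its inputs: the Sample size section claims no gain from adjustment, and the Primary analysis section names only site.

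Two further points carry less weight. The hypothesis is directional, and a one-sided 0.05 test would have 82.6% power; but no one-sided test is declared, and that calculation would give 51. The text is also hedged as approximate, but the same paragraph treats 0.45 as distinct from 0.5, and the hedge does not stretch to 54 against 64.

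It is fair to add that the 73% applies to a two-sided comparison without baseline adjustment, and that the change-score column above is a set of scenarios. The article does not say which SD its effect size refers to.

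**Conclusion.** The concern holds. No reading that uses only the stated inputs gives 54 per arm. For a two-sided 5% comparison without baseline adjustment, the requirement is 64 per arm; 54 per arm gives 73% power at 0.5 and 80% power only at 0.54. If 0.5 refers to the SD of the score and change is analysed without the baseline covariate, power is lower still for correlations below 0.5. The 80% claim is recovered only by adding an assumption the article does not make: baseline-adjusted ANCOVA with a correlation of about 0.40 or more. The mismatch between 54 and 147 in the same paragraph makes it unlikely that a coherent calculation was done and its assumptions merely left out.

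**What to change.** Correct the Sample size section, stating sidedness and the assumed test, in one of two ways:

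- **Unadjusted:** 54 per arm gives 73% power for an effect size of 0.5, and 80% power for 0.54, at two-sided 5%.
- **Baseline-adjusted:** 54 per arm gives 80% power for an effect size of 0.5 at two-sided 5%, assuming ANCOVA adjusted for baseline with a baseline to 6-month BCAPI correlation of at least 0.40. Baseline BCAPI must then be named as a covariate in the Primary analysis section. The correlation needs a source of its own; it should not be chosen because it returns 54.

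In either case, recompute the 0.45 figure on the same assumptions: 79 per arm unadjusted, or 78.49 × 0.84 = 65.9, so 66 per arm, with r = 0.40.

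The cost is wording, plus one covariate in the primary model under the second option. No extra families are needed. The price is that the stated power becomes either somewhat less favourable or explicitly conditional. The article says recruitment is only just starting, so the correction can be made before any outcome data exist.

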### Recruitment

Recruitment will take place over the course of a year at six participating centres, each of which will be required to recruit around 19 families per year. Assuming an uptake rate of 1:3, each centre will be required to refer five women to the study per month, to achieve a total of 114 participants over a year.

Referrals will be made by any worker who has contact with families who are in a drug or alcohol treatment programme including midwives, drug treatment centre workers, staff at children’s centres and staff working with charitable organisations within the field. They will provide eligible families with a brief information sheet inviting them to receive more information about the study, and asking them to provide their consent to pass on their contact details to the research team. The research team will call the family, inform them that they will receive some information in the post and agree to call them in 5 days to answer any questions, and to hear their decision about taking part. Primary carers who are interested in taking part will then be visited by a researcher at home or a venue of their choice to discuss any queries they may have about participation. Participants who agree to take part will be asked to provide written informed consent by initialling, signing and dating a study consent form, which will be witnessed by the researcher. Written informed consent will always be obtained before any study-specific procedures including collection of baseline data. A telephone randomisation procedure will be instigated, and the participants will be contacted within 24 hours of the visit to inform them about their allocated group.

### Data-collection instruments

#### *Primary outcome measures*

*Child abuse potential* will be assessed using the Brief Child Abuse Potential Inventory (BCAPI) [53], which is a 33-item self-report questionnaire developed to identify individuals at risk for physical child abuse, with an agree/disagree format. BCAPI has a 9-item validity scale and a 24-item abuse risk scale. The internal reliability of the full CAPI abuse scale is high, with KR-20 correlation coefficients ranging from .92 to .96 and good test-retest stability of .91 and .83 for 1-day and 1-month intervals, respectively [53]. BCAPI is highly correlated with the full CAPI [54], and has a good inter-item consistency of .88 [55].

#### *Secondary outcome measures*

*Parent–toddler interaction* will be assessed using the infant and toddler versions of the CARE-Index [56]. The CARE-Index requires a 3-minute video of the parent with their child. It measures three aspects of maternal behaviour (sensitivity, covert and overt hostility, and unresponsiveness) and four aspects of a toddler’s behaviour (cooperativeness, compulsive compliance, difficultness and passivity). Scores range from 0 to 14, higher scores indicating better sensitivity and/or co-operation and so on, and the scores for each are interdependent such that a high score for maternal sensitivity is related to a low score for hostility and unresponsiveness. Similarly a high score for infant co-cooperativeness is related to a low score for difficultness, passivity or compulsive compliance. The CARE-Index has been shown to discriminate abusing, neglecting, problematic and adequate dyads [57]. The inter-rater reliability for the infant CARE-Index was 0.75 or above for four of the seven variables. The inter-rater reliability for maternal sensitivity was 0.81, maternal unresponsiveness 0.87, maternal control 0.85, infant cooperative 0.57, infant compulsive 0.96, infant difficult 0.99 and infant passive 0.98 [57].

The toddler version of the CARE-Index will be used with children over 2.5 years of age. This newly developed version of the tool has a good inter-rater reliability of .93 but a rather low test-retest reliability of .40 [58]. There is, however, a significant correlation between the maternal sensitivity score on the toddler CARE-Index and child attachment security using the Preschool Assessment of Attachment classification (PAA) [58,59].

*Infant social and emotional adjustment* will be assessed using the Brief Infant and Toddler Socio-emotional Adjustment Scale (BITSEA) [60], which comprises a 42-item parent-report measure of infant and toddler (that is, 1- to 3-year-old children) social and emotional adjustment. It comprises two subscales – competence and problems measured using a three-point Likert scale. A higher score for the competence subscale and a lower score for the problems subscale indicate better adjustment. It has an inter-rater reliability ranging from 0.55 to 0.78 [60] and internal consistency of .79 for the problems scale and .65 for the competence scale. It has a test-retest reliability ranging from 0.79 to 0.92, and it also discriminates children with clinically significant problems from matched subjects [60]. 

*Parental psychological functioning* will be assessed using the Depression, Anxiety and Stress Scale (DASS-21), which is a 21-item self-report instrument involving a four-point Likert scale designed to measure the three related negative emotional states of depression, anxiety and tension/stress [61,62]. Cronbach’s alphas for the DASS-21 subscales are .94 for depression, .87 for anxiety and .91 for stress [63]. The measure correlates well with other measures of depression, anxiety and stress [64].

*Parenting stress* will be measured using the Parenting Stress Index short form (PSI-SF) [65], which is a well-validated self-report measure comprising 36 items measured using a five-point Likert scale of perceived stress in the parenting role. PSI-SF scores are highly stable over a 1-year period, based on a subsample of 21 abusive parents. Correlations between the first and second assessments are as follows: .61 for the personal distress scale, .75 for the childrearing stress scale and .75 for the total scale [66].

*Emotional regulation* will be measured using the Difficulties in Emotional Regulation Scale (DERS) [67], which is a 36-item self-report measure of difficulties with emotion regulation. Each item is rated on a five-point Likert-type scale that reflects the proportion of time for which an individual exhibits a particular aspect of emotion regulation; higher scores are indicative of greater difficulties with emotion regulation. The scale gives a score for total difficulties with emotion regulation. The instrument also has good test-retest reliability for a 4- to 8-week period of .88 for the total score, and adequate reliability for the six subscales (.69 for non-acceptance, 0.69 for goals, 0.57 for impulse, .68 for awareness, .89 for strategies and .80 for clarity) [67]. DERS has demonstrated good convergence of validity with established measures of emotional dysregulation, negative emotionality, emotional avoidance, worry, panic and generalised anxiety [67-69]. Additionally, DERS has been shown to adequately predict behavioural outcomes believed to be associated with emotion dysregulation, such as intimate partner abuse, self-harm and aggression [67,70]. The validity of the DERS subscales has been established via multiple factor analytic studies [67,70] and by evidence that the subscales are differentially associated with internalising and externalising behaviour [70].

*Severity of borderline personality* will be assessed using the Personality Assessment Inventory – Borderline (PAI-BOR) [71]. The full Personality Assessment Inventory (PAI) comprises 344 items covering constructs most relevant to a broad-based assessment of mental disorders. PAI-BOR focuses on borderline features and is a 24-item self-report questionnaire using a four-point Likert scale with four non-overlapping subscales that measure the essential features of borderline personality disorder: affect instability (BOR-A), identity problems (BOR-I), negative relationships (BOR-N) and self-harm (BOR-S). These four subscales were designed to measure the unique features given by DSM-IV. PAI-BOR has an internal consistency of .84 and a test-retest reliability of .86 over a 3- to 4-week time period [72-74].

*Parental drug/alcohol use* will be confirmed using case records and measured using Timeline Follow-back (TLFB), a widely used calendar-based method of assessment [75]. Each interview is structured using a calendar in which recent events, such as payday social events, are used as memory aids to assist in recall. This is a reliable and valid measure of substance use; patients’ reports of their drug consumption using this method generally had high a retest reliability exceeding .85, convergent and discriminant validity with other measures, agreement with collateral informants’ reports of patients’ substance use, and with results from patients’ urine assays [76]. The number of days of substance use (including amphetamines, cannabis, alcohol and heroin) in the 30 days prior to assessment will be recorded. This self-report will be validated using hair toxicology in a random sample of cases (10%) [77].

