### Data-collection process

Data will be collected by a researcher who is blind to study arm, in the respondent’s home or at a drug treatment centre. Study participants will be requested not to disclose their group allocation to the researcher, and loss of blinding will be recorded and taken into account at the analysis stage. The data will comprise a range of self-report questionnaires that are robust to loss of blinding, and independent observations of the parent and infant, which will be rated externally to the research team. The researcher will provide assistance with the completion of self-report questionnaires where this is required. Data will be collected at baseline, immediately post-intervention and at the 6-month follow-up.

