#### *Subsidiary analyses*

In a similar manner to the primary outcome measures, changes in the secondary outcome measures at baseline and at the 6-month follow-up will also be compared for the intervention groups using ANCOVA. We will also examine the differences at baseline and the immediate post-intervention follow-up period for all outcome measures.

To further investigate the effects of confounding variables, subject to the limitations of the data, we will use multi-level linear mixed modelling between intervention arms. The use of a combination of random and fixed effects, will enable us to model the impact of factors such as therapist, site, family composition and family trajectory.

We will also construct regression models to investigate the relation between the primary outcome measures (that is, CAPI) and other potential mediating variables (that is, measures of parental mindfulness and affect regulation), to address the hypothesis that the impact of the programme on the primary outcome will be mediated via the parent’s capacity for affect regulation.

Multiple imputation (MI) will be used to compensate for missing data at different assessment points. Imputation assumptions for MI will be reported and justified, and imputed data analysed as part of a sensitivity analysis.

Qualitative data will be fully transcribed and analysed thematically using NVivo 8. The limitations of the qualitative data will be assessed in terms of its credibility, transferability, dependability and confirmability [82]. This data will also be examined on a case-by-case basis in terms of the mixed-methods analysis, to better understand the reasons for the success, or otherwise, of the intervention.

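### BITSEA is described for 1- to 3-year-olds, but children enter from before birth, so the planned change score has no in-range baseline for any child under 12 months

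*Protocol article*

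**What the plan says.** All references are to the Protocol article.

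- **Study participants.** The lead inclusion criterion is "They are a primary caregiver with responsibility for a child under the age of 2.5 years". There is no lower age limit. The exclusion of pregnancy has an exception: "Pregnant women (unless the baby is due within 4 weeks of the recruitment period".
- **Secondary outcome measures, BITSEA.** It is the only measure named for infant social and emotional adjustment, and is described as a "42-item parent-report measure of infant and toddler (that is, 1- to 3-year-old children) social and emotional adjustment". No alternative is named for younger children, and its use is not restricted by age.
- **Secondary outcome measures, CARE-Index.** Infant and toddler versions share one description, with scores from 0 to 14. "The toddler version of the CARE-Index will be used with children over 2.5 years of age". "The CARE-Index requires a 3-minute video of the parent with their child".
- **Data-collection process.** "Data will be collected at baseline, immediately post-intervention and at the 6-month follow-up". The article does not say whether the 6 months run from baseline or from the end of the 20-week programme.
- **Subsidiary analyses.** "changes in the secondary outcome measures at baseline and at the 6-month follow-up will also be compared for the intervention groups using ANCOVA". Baseline to post-intervention differences are also planned for all outcomes.

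**The concern.** The article itself fixes the eligible ages, the instrument, the instrument's age range and the form of the analysis, and these do not fit together. A change score needs a usable value at both ends. For a child under 12 months at entry, the baseline end lies outside the range the article gives. The stated analysis must then drop that child or use a score from outside the described age group.

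Reading ANCOVA in its usual sense, with baseline as a covariate, does not help, because the baseline is still needed. A separate analysis plan could change the comparison, but it could not supply an in-range baseline for these children.

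At stake is one of the child outcomes named in the hypotheses. As written, it would be estimated in an unstated, older subset or on scores of doubtful meaning.

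The CARE-Index raises a lesser version of the problem. Entry is under 2.5 years and the toddler version applies over 2.5 years, so every live-born child starts on the infant version. A child who passes 2.5 years before the last visit finishes on the other one.

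**Working it through.** There is no figure in the article to reproduce, so this is age-window arithmetic.

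**Inputs from the article**
- Entry age *a*: under 30 months, no lower limit.
- BITSEA range: 12 months up to either 36 months (third birthday) or 48 months (fourth birthday). The wording allows both.
- CARE-Index switch: above 30 months.
- Programme length: 20 weeks = 140/30.44 = 4.6 months.
- Last visit: *f* = 6.0 months after baseline, or *f* = 4.6 + 6 = 10.6 months.
- Planned sample: 114 families.

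**Assumption.** The age distribution is not given. The main case takes *a* as uniform over 0 to 30 months.

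**Conditions**
- Baseline BITSEA out of range: *a* < 12.
- In-range pair: *a* ≥ 12 and *a* + *f* ≤ upper limit.
- In-range follow-up score: 12 ≤ *a* + *f* ≤ upper limit.
- CARE-Index version change: *a* + *f* > 30.

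**Results, uniform 0 to 30 months**

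| Quantity | *f* = 6.0 | *f* = 10.6 |
|---|---|---|
| Baseline BITSEA out of range | 12/30 = 40% | 12/30 = 40% |
| In-range pair, limit 36 months | (30 − 12)/30 = 60% | (25.4 − 12)/30 = 45% |
| In-range pair, limit 48 months | 60% | (30 − 12)/30 = 60% |
| In-range follow-up score, limit 36 months | (30 − 6)/30 = 80% | (25.4 − 1.4)/30 = 80% |
| In-range follow-up score, limit 48 months | 80% | (30 − 1.4)/30 = 95% |
| CARE-Index version change | (30 − 24)/30 = 20% | (30 − 19.4)/30 = 35% |

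The oldest possible child at the last visit is 30 + 10.6 = 40.6 months, so with a 48-month limit nobody leaves the range at the top.

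Of 114 families, before dropout, about 46 (0.40 × 114) would have no in-range baseline. About 51 to 68 would have a pair, and at least 91 (0.80 × 114) an in-range follow-up score. About 23 to 40 would change CARE-Index version.

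**Sensitivity to the age assumption.** Triangular distributions over −1 to 30 months, a span of 31 months that allows for unborn babies:
- *Younger-skewed:* baseline out of range 1 − (18/31)² = 66%. Version change (6/31)² = 4% to (10.6/31)² = 12%. In-range follow-up score, limit 36 months: (24/31)² = 60% for *f* = 6.0.
- *Older-skewed:* baseline out of range (13/31)² = 18%. Version change 1 − (25/31)² = 35% to 1 − (20.4/31)² = 57%.

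At the extremes, if every child were under 12 months at entry, no BITSEA change score would be in range. If every child were 12 months or older, no baseline would be out of range.

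**The case against.** Several arguments limit this point, and most of them stand.

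- **Many families.** A reader might infer that a large share of the sample is affected. The article gives no ages, so no share can be read from it. The percentages are conditional on the assumed distribution.
- **Loss at the upper end.** A reader might infer that older children outgrow BITSEA by the last visit. That needs both a limit at the third birthday and follow-up counted from the end of the programme. A 3-year-old in ordinary usage is under four, and then no child is lost.
- **CARE-Index change as a difference of two instruments.** The article gives both versions one description and one 0 to 14 scale, and nowhere says that their scores are not comparable. The toddler version's "a rather low test-retest reliability of .40" is disclosed openly and would remain under any analysis. Child age is fixed before randomisation, so switching should be similar in both arms and adds noise rather than bias between them. The text does not support a ban on pooling versions or a need to standardise within version.
- **Economic evaluation.** A reader might infer that its CARE-Index outcome is compromised. That section uses the score at 6 months, not the change, and a version is assigned at every age.
- **Imputation.** A reader might infer that inapplicable scores will be imputed. Multiple imputation is confined to a sensitivity analysis, with its assumptions to be reported and justified.
- **Pregnancy.** Women recruited before birth are a narrow exception (1/31, about 3%, if ages were uniform from −1 to 30 months), and the article does not say when their baseline is taken.

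It can also be said that a condensed article leaves rules on score eligibility to a fuller document. That is fair for handling the CARE-Index version. It does not answer the BITSEA point, because the age range and the change analysis are both stated here and conflict.

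**Conclusion.** The point holds for BITSEA. By the article's own text, every child under 12 months at entry lacks an in-range baseline, and the stated change analysis cannot properly include that child. This needs no assumption about ages, only that such children are enrolled, as eligibility allows.

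The size does depend on ages. Under uniform entry over 0 to 30 months, 40% lack an in-range baseline, against 18% and 66% under the two skewed distributions. The contrast that matters for the remedy is between 45% to 60% of families with an in-range pair and about 80% or more with an in-range 6-month score. That last figure would fall to 60% in the younger-skewed case with follow-up at 6 months from baseline.

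The CARE-Index version change is real but secondary, at about 20% to 35% under the uniform assumption. It calls for adjustment only. BCAPI, the primary outcome, is completed by the parent about the parent, and none of this touches it. The change is worth making, but it does not threaten the trial's main conclusion.

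**What to change.** **BITSEA**
- Replace the change analysis with a comparison of follow-up scores, with arm, site and child age in the model.
- Include children whose age at the *scheduled* visit date is within the instrument's range. Scheduled age does not depend on allocation or on how late a visit happens, so the comparison stays randomised.
- State the exact upper age limit, and whether the 6 months run from baseline or from the end of the programme.
- Do not impute scores outside the range.
- Apply the same rule at the post-intervention visit. Under the uniform assumption, (30 − 7.4)/30 = 75% would be in range there.

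**CARE-Index**
- Analyse the follow-up score on its 0 to 14 scale, with baseline as covariate and adjustment for child age or version.
- Add a sensitivity analysis restricted to children on one version.
- Say when the baseline is taken for women recruited before birth.

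**Cost.** The change needs revised analysis wording and an age rule tied to the visit schedule. The article says recruitment was only about to start, so this comes early enough. The BITSEA comparison would include fewer families than the full sample, and would give up the precision that a baseline score offers where one exists.
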